# Traditional Chinese medicine versus regular therapy in Henoch-Schönlein purpura nephritis in children: study protocol for a randomized controlled trial

**DOI:** 10.1186/s13063-019-3484-3

**Published:** 2019-08-29

**Keywords:** Henoch-Schönlein purpura nephritis, Traditional Chinese medicine, Tripterygium glycosides, Study protocol

## Abstract

**Background:**

Henoch-Schönlein purpura nephritis (HSPN) is the most common secondary glomerular disease in children. Currently, the treatment for HSPN is always selected based on the Kidney Disease Improving Global Outcomes guidelines; however, this approach may lead to undertreatment, especially in patients with persistent proteinuria that does not reach nephrotic levels and/or hematuria and those with a pathological classification between grades 1 and 3 according to the International Study of Kidney Disease in Children. This study was performed to evaluate the curative effect and safety of a traditional Chinese medicine (TCM) integrated treatment program in this type of HSPN.

**Methods:**

This multicenter, open-label, large-sample, randomized controlled trial was performed in China and included 500 children with HSPN exhibiting mild pathological patterns. The treatment group to control group ratio was 2:1, and each group was further stratified into two types, light and heavy, according to urinary protein quantification and pathological type. The treatment group received tripterygium glycosides (TGs), tanshinone IIa sodium sulfonate injection, and Chinese herbs selected based on syndrome differentiation in TCM. The heavy and light subgroups received treatment courses and dosages of TG. In the control groups, the light group received benazepril hydrochloride tablets, low molecular weight heparin calcium injection, dipyridamole tablets, and a Chinese medicine placebo, while the heavy group received the same treatment plus prednisone. All groups were treated for 3 months and then followed up for 9 months. The efficacy and safety of the treatments were then evaluated among the groups.

**Discussion:**

Currently, few treatments are available for HSPN patients with mild pathological patterns indicating light to moderate proteinuria and/or hematuresis. In this large-sample study, we provide a new approach for HSPN that includes an integrated treatment program that incorporates TCM.

**Trial registration:**

Clinical Trials.gov, NCT03591471. Re-registered on 19 July 2018.

**Electronic supplementary material:**

The online version of this article (10.1186/s13063-019-3484-3) contains supplementary material, which is available to authorized users.

## Background

Henoch-Schönlein purpura nephritis (HSPN) is one of the most common secondary glomerular diseases in children (78.9%) [1]. Approximately 30–50% of patients diagnosed with HSP develop HSPN, with risk depending on clinical manifestations [2, 3]. Although most patients with HSPN have a good chance of achieving a recovery, approximately 10–20% of patients with moderate to heavy proteinuria are at risk of kidney failure [4–6]. Therefore, it remains necessary and important to obtain an early diagnosis, to implement the right treatment strategy, and to perform long-term follow-up [7].

HSPN presents with diverse clinical manifestations, including microscopic hematuria, microalbuminuria to massive proteinuria, nephrotic syndrome (NS), acute rapidly progressive glomerulonephritis (RPGN), and acute renal insufficiency (ARI). There are also six pathological grades that are differentiated according to the International Study of Kidney Disease in Children (ISKDC) classification [8]. The current treatment strategy for HSPN is mainly based on the Kidney Disease Improving Global Outcomes (KDIGO) guidelines [9]: angiotensin-converting enzyme inhibitors (ACEIs) and/or angiotensin receptor blockers (ARBs) are recommended for use in patients with HSPN with persistent proteinuria ranging from 0.5 to 1 g/day/1.73 m^2^; while for those with persistent proteinuria (> 1 g/day/1.73 m^2^) after treatment with ACEI/ARBs and a glomerular filtration rate above 50 ml/min/1.73 m^2^, a 6-month course of corticosteroids should be used. In patients with clinical features such as massive proteinuria, NS, or RPGN or with an ISKDC grade above IIIb, we administer both steroids (prednisone and methylprednisolone) and immunosuppressive agents (cyclophosphamide, azathioprine mycophenolate mofetil, and calcineurin inhibitors). However, the KDIGO guidelines for treatment of HSPN are graded with low strength and very low quality of evidence (the recommendations were graded 2D), which were for the large part extrapolated from adult trials in IgA nephropathy, not HSPN. In addition, treatment with platelets and anticoagulants remains controversial, but the evidence-based guideline in China indicates that the addition of anticoagulants and/or antiplatelet aggregation agents could also be used to treat HSPN [10].

It is widely believed that the prognosis of HSPN depends on the severity of kidney injury, with more crescents indicating a worse outcome. Otherwise, there is a lack of high-quality data to inform treatment decisions in any subtype of HSPN, particularly in those with low-grade proteinuria or less severe pathologic classification. However, a recent study explored long-term renal prognoses in patients with grade II and no crescents, and found that 25% of these individuals retained proteinuria and thus were at continued risk of developing chronic renal failure over time [11]. Some experts have noted that the current treatment strategy for HSPN is insufficient if only the KDIGO guidelines are followed, especially in patients with mild types of lesions [11]. There are two probable reasons for this view. First, it is possible that acute glomerular inflammation previously occurred but was not treated in an accurate or timely manner. Second, even patients with minimal renal symptoms can progress to a manifestation similar to IgAN, in which proteinuria is slowly progressive and NS is less frequent [12].

It is therefore necessary to seek alternative and supplementary therapies to treat HSPN exhibiting a mild pathological pattern. Finally, we found that traditional Chinese medicine (TCM) therapy represents a new method for treating patients in this situation.

Tripterygium glycoside (TG) is the active ingredient in triptolide and a patented TCM derived from *Tripterygium wilfordii* Hook. It is sometimes used as a type of immunosuppressant in children with HSPN. A meta-analysis including 46 RCTs reported that the total effective rate (reduction of clinical symptoms and proteinuria/urinary occult blood) was better in the TG group than in a conventionally treated glucocorticoid (GC) group (RR = 1.36, 95% CI = 1.14 to 1.62; RR = 1.30, 95% CI = 1.16 to 1.46), and the time required for proteinuria and hematuria disappearance was shorter in the TG group than in the conventional treatment GC group by an average of 9 days (95% CI = – 11.99 to − 6.01; MD = – 12.00, 95% CI = – 16.13 to – 7.87) [13].

Tanshinone IIA is the main component of danshen (*Salvia miltiorrhiza*). Two studies [14, 15] reported that the therapeutic effects were better in a group treated with tanshinone IIA sulfonic acid sodium injection (TIIa) combined with GC than in the group treated with GC alone. Two other studies [16, 17] also found that TIIa combined with TG produced a higher level of decline in D-dimer and fibrinogen (FIB), and a longer prothrombin time (PT) at 4 weeks and 12 weeks than were observed in a TG group.

Qingrezhixue granule is a type of hospital preparation based on related TCM therapy that was first proposed by [name] and is made by the Affiliated Hospital of Henan University of TCM (Patent No. 2018 1011 8156.8). Each packet of granules contains the following drugs: Dihuang (*Rehmanniae radix*), Mudanpi (Cortex Moutan), danshen (*S. miltiorrhiza*), hanliancao (*Eclipta alba*), Chishao (*Radix paeoniae* Rubra), Sanqi (*Panax notoginseng*), xiaoji (*Herba cirsii*), and qiancao (Radix Rubiae). Unlike modern medicine, TCM is based on syndrome differentiation and is determined according to clinical manifestations and physical conditions. For example, the [name] “primary syndrome” and “secondary syndrome” system classifies five TCM patterns of syndromes: wind heat complicated with blood stasis, blood heat complicated with blood stasis, dampness heat complicated with blood stasis, yin deficiency complicated with blood stasis, and both qi and yin complicated with blood stasis [18]. Qingrezhixue granules play a key role in clearing heat and cooling blood, thereby promoting blood circulation and removing blood stasis. Other herbs can also be added if necessary according to the type of syndrome.

We achieved good results by combining these comprehensive treatment programs with TCM. In our previous multicenter randomized controlled study performed in children with HSPN with proteinuria and hematuria, and renal pathology between grade I and grade III (crescents < 25%) by ISKDC classification (172 cases), we designed a 12-week course of treatment with no follow-up and found that, compared to patients treated with routine therapy (GC + benazepril LMWHC + dipyridamole), the TCM-treated group (TG + Xiangdan injection + Qingrezhixue granules) exhibited better curative effects in alleviating proteinuria (χ^2^ = 9. 5585, *P* = 0. 0227; χ^2^ = 15. 4872, *P* = 0. 0014) at 4 and 8 weeks, and reduced RBC in urine (χ^2^ = 7. 9638, *P* = 0. 0468) at 8 weeks, without any serious adverse reactions [19]. Based on a preliminary study, we further optimized the design scheme, enlarged the sample size, amplified the applicable clinical syndrome types, and divided the patients into two groups with two subgroups each according to the level of proteinuria. The different treatments were compared to evaluate the efficacy and safety of a TCM stepped care program in HSPN.

## Methods/design

### Study aim

Because regular therapies are currently insufficient, the aim of this study was to provide an alternative TCM program for children with HSPN with hematuria associated with proteinuria and isolated proteinuria. The study aimed to provide an appropriate reference dose of TG tablets for children through this comprehensive research program of TCM.

### Study design

This study will be a stratified, randomized, multicenter, open-label controlled prospective trial. The flow diagram is shown in Fig. 1.

**Fig. 1 Fig1:**
[figure not shown]
Flow diagram

### Study setting

The patients will be recruited in six class III grade I hospitals, including one sponsor (the First Affiliated Hospital of Henan UTCM) and five collaborator (Peking University First Hospital, Children’s Hospital of Fudan University, Children’s Hospital of Shanghai, Affiliated Hospital of Chengdu UTCM, and Affiliated Hospital of Yunnan UTCM) institutions. All included cases must be hospitalized.

As a responsible party, the 450-bed pediatrics department of the First Affiliated Hospital of Henan UTCM is a national key specialty department focused on HSPN. Additionally, the department has rich experience in treating various types of HSPN using combinations of TCM and western medicine, especially with regard for TG. Annually, approximately 20,000 outpatients visit, and approximately 2300 inpatients are hospitalized in the pediatric nephropathy and purpura wards. In addition, the open access of the pediatric renal pathology laboratory is convenient for patients.

The conditions described lay a solid foundation for the feasibility of this trial.

### Participant recruitment

We expect to recruit 500 eligible patients from seven hospitals in different regions of China. Parental consent will be obtained for all enrolled patients. All enrolled patients must be hospitalized in the first 2 weeks of treatment. No further recruiting measures will be taken, and no individuals with a direct relationship to the researchers, such as students/staff of the hospital or close relatives, will be included. Patient enrollment started in September 2014 and is scheduled to end in December 2018.

### Inclusion criteria

Clinical manifestation as proteinuria at non-nephrotic levels with or without hematuria in HSPN.In children with HSPN, total urine protein at 24 h higher than 500 mg or 25 mg/kg or lower than 50 mg/kg or 3.5 g resulting in classification as light type or heavy type, respectively, according to the amount of proteinuria. Patients are biopsied if presenting 24-h protein above 1 g/day/1.73 m^2^. The renal biopsy classification can be used as a reference, and the results of urinary protein quantification (heavy vs light) are used as the basis for classification when these two criteria are conflicting (details presented in Table 1):
Light HSPN: total urine protein at 24 h between 25 and 35 mg/kg, a renal pathological grade less than II, or IIIa with a ratio of crescents, loop necrosis, and adhesion of glomerular and renal capsules less than 10%.Heavy HSPN: total urine protein at 24 h between 35 and 50 mg/kg, a renal pathological grade of IIIb or IIIa and a ratio of crescents, loop necrosis, and adhesion of glomerular and renal capsule higher than 10%.
3.If undergoing kidney biopsy, a renal pathological grade between I and III based on the ISKDC classification with a ratio of crescents, loop necrosis, and adhesion of glomerular and renal capsules lower than 20%.4.Treated with any of five TCM syndrome differentiation types, including wind heat complicated with blood stasis, blood heat complicated with blood stasis, yin deficiency complicated with blood stasis, both qi and yin deficiency complicated with blood stasis, and damp heat with blood stasis.5.Age 2–18 years.6.Disease onset within 2 months.7.Abnormal urine tests for more than 1 week.8.No use of GC and immunosuppressors, such as TG, cyclophosphamide, or mycophenolate mofetil, due to an abnormal urine test.9.The patient or their statutory guardian agrees to participate and provides informed consent.

**Table 1 Tab1:** The subtype classification in this study

Type	24-h protein (main reference)	Biopsy (secondary reference)
Light	25 mg/kg (or 500 mg)–35 mg/kg	A renal pathological grade less than II, or IIIa with a ratio of crescents, loop necrosis, and adhesion of glomerular and renal capsules < 10%
Heavy	35 mg/kg–50 mg/kg (or 3.5 g)	A renal pathological grade of IIIb or remains IIIa with a ratio of crescents, loop necrosis, and adhesion of glomerular and renal capsule > 10%

Note: Results of 24-h protein are used as the main basis for classification (heavy vs light) when these two criteria are conflicting

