Diagnostic criteria	2 main symptoms of blood heat (or 1 main symptom + 2 secondary symptoms) + 1 main symptom of blood stasis

**Table 3 Tab3:** Observation protocol to be followed during treatment and follow-up

Observed indicator/week		Treatment stage (week)								Follow-up stage (week)								
		0	1	2	4	6	8	10	12	16	20	24	28	32	36	40	44	48
Main	24-h urinary protein quantity	×	×	×	×	×	×	×	×	×	×	×	×	×	×	×	×	×
Secondary	Urine red blood cells	×	×	×	×	×	×	×	×	×	×	×	×	×	×	×	×	×
Security	Routine blood tests	×	×	×	×	×	×	×	×	×	×	×	×	×	×	×	×	×
	Hepatic and renal function	×	×	×	×		×		×		×		×		×		×	×

2.Follow-up stage (12–48 weeks).

The 12-week treatment stage will be followed by a 36-week follow-up stage. The main aim of the follow-up is to monitor a series of laboratory indicators and determine the disease recurrence rate. The details are presented in Table 2.

In patients who meet the clinical control standards after 12 weeks of treatment, medication will be stopped and the patients will begin follow-up. The clinical control standards mean that RBC counts and 24-h protein in urine are at normal levels, and urine routine examinations are negative for protein and occult blood. For those patients who do not meet the clinical control standards by 12 weeks, other treatment options could be appropriately selected in the professional judgment of the clinicians. The clinicians who are evaluating the follow-up laboratory results (and determining whether there is a relapse or whether the patient has reached clinical control standards) are not blinded to the patient’s treatment assignment. The criteria for efficacy evaluation are presented in Table 4.

**Table 4 Tab4:** Criteria for efficacy evaluation

Primary outcome	Clinical control rate	Significant efficiency	Effective rate	Ineffective rate
PRO in urine	Negative	PRO decreased by 2+	PRO decreased by +	PRO decreased less than +
	24-h urinary protein quantity is normal	24-h urinary protein quantity reduced > 50%	24-h urinary protein quantity reduced between 30 and 50%	24-h urinary protein quantity reduced < 30% or no change
RBC in urine	U-OB: negative	U-OB: RBC reduction ≥ ++/HP	U-OB: RBC reduction ≥ +/HP	U-OB: no improvement or aggravation in RBC
	RBC ≤ 5/HP	RBC count decreased By > 50%	RBC count decreased between 30 and 50%	RBC count decreased < 30% or no change
Total therapeutic effect	Meet all these requirements	Meet all these requirements	Meet all these requirements	Meet all these requirements

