### Outcomes

The study will be conducted over a period of 1 year (48 weeks) and will include a treatment period of 3 months (12 weeks) and an observation period of 9 months (36 weeks). In all, one primary outcome indicator, one secondary outcome indicator, and four security indexes will be analyzed:
Primary outcome indicator: 24-h urinary protein quantity.

Any change in total urine protein level at 24 h will be assumed to directly reflect a therapeutic effect; hence, this clinical laboratory index should be recorded every 2 weeks during the treatment period and every 4 weeks during the follow-up period (17 times in total). In addition, creatinine excretion measured vs expected for gender will be detected at the same time to verify the adequacy of 24-h urine collection indirectly.

Total urine protein at 24 h is the most important outcome. In previous studies, we found that the improvement of urinary protein of TG at week 4 and week 8 was better than that of the control group, while the difference at week 12 was not significant. Based on these subtypes, this study will further explore the difference in treatment between the two groups. Therefore, we will set 17 nodes, including the treatment period and the follow-up period, to compare the differences in urine protein between the two groups at each node, rather than only retaining the last result at 48 weeks.
2)Secondary outcome indicator: red blood cells in urine.

Compared to the primary indicator, the urine red blood cell count is considered secondary because urine red blood cells recede more slowly than protein recedes. This clinical laboratory index should be recorded at the same points during treatment and follow-up as the primary outcome indicator (17 times in total).
3)Security indexes.

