### Sample size calculation

The previous clinical results showed that the clinical control rate of proteinuria was 48.6% in the TCM group and 35.7% in the western medicine group during the 4th week of treatment. Based on these results, in this study, the total sample size was calculated as 405 cases if the TCM group and the western group were included at a ratio of 2:1. The δ value between them is expected to be 15% with a significance level of α = 0.05 and an assurance of 1 – β = 90%. We will increase the sample size by approximately 20% to reach 500 cases in consideration of the possibility that some patients could miss visits due to the long illness course and follow-up time. Clinical experience indicate that heavy patients will account for approximately 25% of eligible individuals; hence, 120 patients with heavy HSPN and 380 patients with light HSPN will be included.

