### Statistical analysis

All statistical analyses in the study will be carried out by a third party, the Chinese Academy of Traditional Chinese Medicine, using SAS version 6.12, which is validated software for clinical studies. Logistic regression is used to show a difference in the prevalence of clinical control/remission in both groups, including age, gender, place of residence, parents’ educational background, and so on. For the outcome “time from positive to negative for urinary protein and urinary occult blood”, a Cox proportional hazards model is used. The incidence is described for adverse events and Fisher’s test will be used for comparison. Besides, groups and time of therapy on curative effect will be considered. If there are interaction effects between groups, simple effect analysis is performed; if not, grouping effect/time of therapy on curative effect should be considered separately.

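### The Table 4 grades for urine red cells set no baseline condition, so children enrolled without haematuria fit two opposite grades and dilute the secondary comparison

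*Protocol article*

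**What the plan says.** The Study aim section names the target population as "children with HSPN with hematuria associated with proteinuria and isolated proteinuria", and the Inclusion criteria admit "Clinical manifestation as proteinuria at non-nephrotic levels with or without hematuria in HSPN". Children without haematuria are therefore an intended part of the trial.

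The Outcomes section lists one secondary efficacy measure: "Secondary outcome indicator: red blood cells in urine", recorded at the same 17 visits as the primary outcome.

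Table 4 (Intervention section) gives urine RBC its own row with four grades:
- Clinical control is an absolute state: occult blood negative and RBC ≤ 5/HP.
- The two middle grades are reductions from a starting value (more than 50%, and 30 to 50%).
- The lowest grade, ineffective, includes "RBC count decreased < 30% or no change".

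The text before Table 4 adds "The clinical control standards mean that RBC counts and 24-h protein in urine are at normal levels", together with a routine urine test negative for protein and occult blood.

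The Statistical analysis section says "Logistic regression is used to show a difference in the prevalence of clinical control/remission in both groups", and assigns a Cox model to "time from positive to negative for urinary protein and urinary occult blood". No section ties the RBC grades to the child's urine RBC at week 0.

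**The concern.** An RBC response grade carries information about treatment only in a child who has red cells to clear. A child with none at week 0 already satisfies the top grade. The same child shows no change, which is the bottom grade. The percentage-reduction grades have no meaningful starting value to fall from. The written rule therefore gives two contradictory answers for a population that the protocol sets out to enrol.

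Whichever answer is used, these children contribute nearly the same result in both arms, and a real effect on haematuria becomes harder to see. If they are scored as control, the reported control rates also overstate how often haematuria cleared.

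**Working it through.** **The plan's own figure.** The Sample size section states that "the clinical control rate of proteinuria was 48.6% in the TCM group and 35.7% in the western medicine group" at week 4, plans on a difference of 15 points with α = 0.05 and 90% power at 2:1, and arrives at 405. With p_C = 0.357 and p_T = 0.357 + 0.15 = 0.507, the unpooled formula for the control arm is

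n_C = (z_α + z_β)² × [p_C(1−p_C) + p_T(1−p_T)/2] / 0.15².

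A one-sided α of 0.05 gives n_C = 135, hence 3 × 135 = 405, which matches. A two-sided α gives n_C = 166, hence 498. The sizing concerns proteinuria. The article gives no sizing for urine RBC and no share of children without haematuria.

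**Assumptions for the illustration.**
- The share f without haematuria at week 0 is 10% to 40%. This range is assumed.
- Among children with haematuria, the RBC control rates equal the planning rates for proteinuria, 50.7% and 35.7%.
- There are 500 children, split 333:167, and the test is two-sided at 5%.
- Children without haematuria at week 0 stay without it.

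**Formulas.**
- Scored as control: each arm's rate becomes f + (1−f)p, a rise of f(1−p).
- Scored as ineffective: each arm's rate becomes (1−f)p.
- In both cases the difference is (1−f) × 0.15.
- Restricted to children with haematuria: the rates and the 15-point difference stay, and the arm sizes become 333(1−f) and 167(1−f).
- Power = Φ(difference/SE − 1.96), where SE² is the sum over arms of rate × (1−rate)/n.

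**Worked case, f = 20%.**
- Scored as control: 0.2 + 0.8 × 0.507 = 60.6% and 0.2 + 0.8 × 0.357 = 48.6%. The difference is 12.0 points, SE 0.0470, power Φ(0.591) = 72.3%. The rise is 0.2 × 0.493 = 9.9 points in the TCM arm and 0.2 × 0.643 = 12.9 points in the control arm. The larger rise in the lower-rate arm is what closes the gap.
- Scored as ineffective: 40.6% and 28.6%, SE 0.0441, power 77.7%.
- Haematuria subset: about 266 and 134 children, SE 0.0515, power 82.9%.

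| f | Difference, all children | Power, scored as control | Power, scored as ineffective | Power, haematuria subset |
|---|---|---|---|---|
| 10% | 13.5 points | 82.1% | 84.6% | 87.0% |
| 20% | 12.0 points | 72.3% | 77.7% | 82.9% |
| 30% | 10.5 points | 61.7% | 69.4% | 77.7% |
| 40% | 9.0 points | 51.2% | 60.3% | 71.2% |

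**Sensitivity.** A formula with pooled null variance agrees within about 2 points for children scored as control and for the subset (81.5% to 52.5%, and 85.9% to 69.5%). For children scored as ineffective it is up to about 3.5 points lower (83.2% to 56.9%). With only 405 evaluable children, the pooled formula gives 72.9% to 44.6% (scored as control) and 77.9% to 60.2% (subset). The order does not change.

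**Is the RBC row likely to be tested alone?** The Background section reports a separate RBC comparison at 8 weeks from the group's earlier trial, χ² = 7.9638 with P = 0.0468. That P value corresponds to 3 degrees of freedom, as in a table of two arms by four grades. This makes a stand-alone test of the row plausible. It does not prove that one is planned.

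**The case against.** The strongest objection is that no written analysis clearly tests the RBC row alone. The logistic regression is for clinical control or remission, and the control standard before Table 4 is a composite of normal protein and normal RBC. A child with isolated proteinuria fails that composite at week 0. A reader might infer that these children are automatic successes in the logistic regression, but the document does not support that. The point is confined to the RBC row of Table 4 used as the secondary outcome.

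Other objections stand in part:
- A reader might infer that the Cox outcome is also broken. It is not, because a time from positive to negative already presupposes a positive start.
- Scoring as success is not fixed by the document, since the ineffective grade fits too. Both scorings dilute the difference.
- A child who develops haematuria later leaves the control grade, so these children are not wholly uninformative.
- The prevalence of normal urine RBC among all randomised children is a legitimate quantity. It is not a measure of response, however, and Table 4 is headed as efficacy criteria.
- The week-4 proteinuria rates are a stand-in, and the Outcomes section itself says that red cells recede more slowly than protein.

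Finally, one may say that the denominator belongs in the statistical analysis plan, which is not shown. That would answer a mere omission. Here the protocol itself fixes the eligibility and the grades, and together they assign an intended population two opposite results.

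**Conclusion.** The point holds for the RBC response grades. For any f above zero, the between-arm difference in RBC response is reduced to (1−f) of its size under either scoring. Scoring as control also raises both reported rates by f(1−p), which is more in the lower-rate arm.

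The loss in power depends on f. Compared with the haematuria subset, scoring all children as control costs about 5 points of power at f = 10% and 20 points at f = 40%. These sizes rest on an assumed share and on proteinuria rates used in place of RBC rates, so they are an illustration and not an estimate for this trial.

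A reader might infer bias toward one arm or a threat to the main result. Neither follows: f is expected to be equal in randomised arms, the effect is toward the null, and the primary 24-h protein outcome is unaffected. This is a moderate defect in the definition of the only secondary efficacy outcome.

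**What to change.** Add one sentence to Outcomes or Statistical analysis: the Table 4 RBC response grades apply only to randomised children with RBC > 5/HP or positive occult blood at week 0. Report new haematuria in the remaining children separately by arm. The Cox outcome needs no change beyond using the same week-0 definition of positive.

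The subset is defined by a measurement taken before randomisation, so the randomised comparison is kept. Table 3 already schedules urine RBC at week 0, so no new data are needed. Because the Trial status section says that the data are in the statistical stage, the sentence should be dated and should state whether RBC results by arm had been seen.

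The cost is a smaller denominator for the secondary outcome. In the illustration, the undiluted 15-point difference more than repays it at every share examined.
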